### Participants

A total of 144 participants (randomized in two intervention groups and one control group) will be included in this study. The study will be conducted in the Central Catalonia health area (Spain). Participants will be recruited from Monistrol de Montserrat *Primary Care Center* (CAP), Vic Sud CAP (Vic), CAP les Bases (Manresa), Hospital *Sant Bernabé* (Berga) and Anoia CAP (Igualada).

Inclusion criteria for eligibility will include participants (i) with T2DM, (ii) that have no major physical limitations prescribed by the doctor or any HCP and (iii) that are physically inactive according to the Spanish version of a Brief Physical Activity Assessment Tool – SBPAAT screening tool [44]. Participants will be excluded if they (i) are pregnant or have T2DM due to gestation; (ii) are unable to freely consent to take part in the study; (iii) are unable to understand the study materials or PA intervention; (iv) have complications such as neuropathy, retinopathy and nephropathy; (v) have relative or absolute contraindications to do PA; and (vi) have a body mass index over 34.9 kg/m^2^ since Nordic walking uses poles that require free arm mobility that is impaired by a body mass index over 35 kg/m^2^.

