### Sample size

We calculated the sample size (*n* = 144) in relation to the drop-out ratio in PA interventions showed by other studies (15%) [45] with a balanced one-way analysis of variance power calculation of 80%, a significance level of 5%, an expected drop-out rate in participants of 15% and an effect size of 0.5. As a result, 48 participants will be needed in each group in the three-arm randomized controlled trial.

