### Randomization and blinding

A computerized random-number generator (http:// www.randomization.com, created by [name], Tufts University) will be used to randomize eligible participants at the level of the individual participant, stratified by sex and age, in blocks of ten.

Concealed randomization will be conducted by the research member after each participant has been included in the study, has been assigned an identification code and has completed the study baseline assessment. Nurses from CAPs/Hospitals will enrol the participants.

Allocation concealment will be ensured as the random-number generator will not be released until the patient has been recruited into the trial, which takes place after all baseline measurements have been completed. Participants will be notified personally face-to-face.

The design is open label with only outcome assessors being blinded so unblinding will not occur. The researchers carrying out the baseline assessments will be blind to group allocation. The statistician will also be blind to group allocation until the completion of the statistical analysis. Participants will be asked not to reveal group allocation when undergoing follow-up measurements. To assess the extent to which blinding has been preserved, researchers will record the number of cases in which allocation was revealed.

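### Blocks of ten do not fit a three-arm trial planned at 48 per arm: no full block can be balanced, and no rule for the tenth place is given

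*Protocol article*

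**What the plan says.** Under Randomization and blinding, the protocol article says that a computerised generator will "randomize eligible participants at the level of the individual participant", "stratified by sex and age, in blocks of ten". The Participants section describes "A total of 144 participants", "randomized in two intervention groups and one control group". The Sample size section rests on a "balanced one-way analysis of variance power calculation of 80"% and concludes that "48 participants will be needed in each group in the three-arm randomized controlled trial".

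The target ratio is therefore 1:1:1, although it is not written as a ratio. The article names no unequal allocation, no other block size and no rule for the place left over when ten is divided by three. It does not give the age bands used for stratification, so the number of strata is unknown.

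**The concern.** Permuted blocks are used so that the arms return to the planned ratio at the end of every full block, within every stratum. That works only if the block size is a multiple of the sum of the ratio, here three. With blocks of ten, every full block leaves one arm ahead by one, and the article does not say which.

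Two things are at stake. First, the printed rule and the printed design disagree: either the list was not built as described, or the trial has a ratio rule that is not declared. Second, the arm sizes depend on the missing rule. If the extra place moves between arms, they drift apart by a few participants. If it always falls to one arm, the trial is in effect 4:3:3, and the comparison between the other two arms is smaller than planned. The point concerns the allocation ratio only.

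**Working it through.** **Inputs from the article.** Three arms, 144 participants and 48 per arm (Participants; Sample size); block size ten, stratified by sex and age (Randomization and blinding); 80% power, "a significance level of 5"%, "an expected drop-out rate in participants of 15"% and an effect size of 0.5 whose metric is not stated (Sample size).

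**Assumptions.** Blocks are filled as evenly as possible (4:3:3). There are four strata (two sexes by two age bands), either of exactly 36 each or of random size with equal expected shares.

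**Step 1: the plan's own figure.** The 48 per arm does not reproduce. A three-group ANOVA at 5% and 80% power needs 14 per arm if 0.5 is Cohen's f (17 after dividing by 0.85 for drop-out) and 53 if f = 0.25 (63 after drop-out). That is a separate matter. Here it means only that power has to be shown for assumed effects.

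**Step 2: block arithmetic.** 10 = 3 × 3 + 1, so the most even full block is 4:3:3. Also 144 / 10 = 14.4, so the total is not a whole number of blocks. By contrast 144 / 6 = 24 and 144 / 9 = 16, and full blocks of six or nine split 2:2:2 or 3:3:3.

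**Step 3: arm sizes over 144 participants, four strata (simulation).**

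| Rule | Exactly 48:48:48 | Median gap, largest minus smallest arm |
|---|---|---|
| Ten, extra place rotating | about 7% (strata of 36), 9% (random strata) | 3 |
| Ten, extra place random | about 4% | 5 (strata of 36), 4 (random strata) |
| Ten, extra place always in one arm | never | 15 |
| Six and nine in random order | about 19% (strata of 36), 14% (random strata) | 2 |

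In the first two rows the expected size is 48 in each arm. In the third it is 144 × 0.4 = 57.6 and 144 × 0.3 = 43.2 in each of the other two.

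**Step 4: power if the extra place moves between arms.** Take 46/48/50, a gap of 4. ANOVA power, over all assignments of sizes to arms:
- means 0, 0, 0.5 SD: 0.708 at 48/48/48; 0.698 to 0.717 at 46/48/50;
- means 0, 0.25, 0.5 SD: 0.574 at 48/48/48; 0.565 to 0.584 at 46/48/50.

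The change is about one point in either direction.

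**Step 5: power if one arm always takes the extra place.** The variance of a difference in means is proportional to 1/n₁ + 1/n₂.
- 48 v 48: 2/48 = 0.0417.
- The two smaller arms: 2/43.2 = 0.0463, up 11%.
- Larger v smaller arm: 1/57.6 + 1/43.2 = 0.0405, down about 3%.

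A standardised difference of 0.578 has 80% power at 48 per arm in a two-sided 5% t-test. This value was solved for and is not in the article. The same difference has about 76% power between the two smaller arms and about 81% in each of the other two contrasts. ANOVA power at 58/43/43 is 0.680 to 0.744 (means 0, 0, 0.5 SD) or 0.526 to 0.590 (means 0, 0.25, 0.5 SD). The worst loss is about 5 points, and some assignments gain. If 0.5 is Cohen's f, power stays above 0.999 at either set of sizes.

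**The case against.** A reader might infer that the rule makes 48 per arm impossible and so invalidates the balanced ANOVA behind the power. The article does not support that. If the extra place rotates or is random, the expected size is 48 in each arm, and exact balance does sometimes occur. The word balanced describes the sample size calculation. The planned two-factor ANOVA and linear mixed models do not need equal arms.

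A reader might also take 76% as the power of the trial. It belongs to one contrast out of three, under a fixed extra place that nothing in the article suggests, and the other two contrasts gain a little. If SENWI were the larger arm, both of its comparisons would improve.

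Nor would a better block size guarantee 48:48:48. With blocks of six only or nine only, exact balance is certain if every stratum holds exactly 36, which nothing in the article ensures. With strata of random size it occurs in about 17% and 12% of trials, because final blocks are left incomplete. On the median gap, rotating blocks of ten are close to multiples of three (about 3 against 2).

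All of this stands and limits the size of the point. It does not remove the mismatch. The article chose to print a block size, and that size does not fit the three equal arms printed elsewhere in it. This is a stated value that conflicts with the design, not a detail left to a fuller document.

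**Conclusion.** The point holds as a mismatch between the stated allocation rule and the stated design. The arithmetic is certain: no full block of ten can be balanced over three arms, and the text gives neither a ratio nor a rule that would resolve it. The consequence is small under a moving extra place, a gap of a few participants and about one point of power. It is moderate only in the unstated case of a fixed extra place. Randomised comparisons stay unbiased in every case.

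The sizes rest on four strata with equal expected shares, on 4:3:3 filling and on the illustrative effects used above. It is worth correcting because the defect is definite and the remedy costs almost nothing.

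**What to change.** First establish how the list in use was built.

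- **If it uses blocks of ten:** for everyone not yet randomised, change to block sizes that are multiples of three, for example six and nine in random order within each stratum. Imbalance then comes only from incomplete final blocks (median gap about 2; exact balance not guaranteed). Report the arm sizes already produced by the existing list.
- **If it already uses a multiple of three:** correct the sentence on block size.
- **If 4:3:3 is intended:** state that ratio and which arm takes the extra place, and restate the planned arm sizes and power to match.

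The cost is one sentence in the protocol and, where needed, a new list from the same generator. The Trial status section reports 40 of 144 enrolled at submission, with four of the five sites yet to start. At that date up to 144 − 40 = 104 allocations could still have followed a corrected list.

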### Study interventions

A three-arm randomized controlled trial will assess the impact of a primary care-based PA intervention implementing SENWI against an isolated NW programme (comparison group 1) (see Fig. 1) and usual PA advice (e.g. to walk) provided by HCPs (comparison group 2).

**Fig. 1 Fig1:**
[figure not shown]
Schedule of the socio-ecological with Nordic walking intervention (SENWI) and Nordic walking intervention (NW). PA, physical activity

All instructors in charge of conducting the SENWI and NW interventions will undergo a standardized protocol. Both intervention (NW and SENWI) sessions will be implemented in the surroundings of the different CAP/hospital facilities (green areas or parks).

To assess safety and well-being during the period of the intervention, patients’ perceptions about health, injury, pain and intervention will be asked every week by a specially trained professional physiotherapist in charge of delivering the NW.

All participants will continue with their pharmacological treatment plan and nutritional and PA recommendations provided by the treating HCP. Moreover, all three interventions have no expected harmful effects as they only involve low- and moderate-intensity PA. However, it may be possible that some patients feel discomfort in the first weeks of the intervention. To deal with that, we propose a protocol that starts with less time and intensity and gradually increases. Also, instructors will be formed by HCPs (i.e. nurses) about hypoglycaemias and how to deal with it in case an event occurs.

Adverse events that the participant attributes as “study-related” will be collected at each follow-up assessment in both groups’ intervention. Healthcare use (number of visits to HCP) pertaining to the adverse event(s) will also be measured by research team members asking patients directly. To register healthcare use pertaining to adverse event(s), patients will be asked directly by research team members.

Adherence will be monetarised through attendance at the session schedule. Phone calls will be used to improve adherence to interventions.

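### Formal adverse-event collection is limited to events the participant attributes to the study and, on the likelier reading, to the two walking arms, so harms have no usual-care comparator

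*Protocol article*

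**What the plan says.** The trial has three arms: SENWI, NW alone and usual advice. The Sample size section states that "48 participants will be needed in each group in the three-arm randomized controlled trial", which gives 144 in all.

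Safety is covered in Study interventions, in the text after Fig. 1. Four statements matter:

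- **Premise.** The article states that "all three interventions have no expected harmful effects as they only involve low- and moderate-intensity PA". It adds that some early discomfort is possible.
- **Weekly enquiry.** During the intervention period "patients’ perceptions about health, injury, pain and intervention will be asked every week", and this is done "by a specially trained professional physiotherapist in charge of delivering the NW".
- **Formal rule.** "Adverse events that the participant attributes as “study-related” will be collected", and the sentence continues that they "will be collected at each follow-up assessment in both groups", ending with the word intervention.
- **Healthcare use.** HCP visits are recorded by asking patients, but only visits that pertain to those adverse events.

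The usual-advice section describes no adverse-event enquiry. The follow-up assessments T1, T2 and T3 fall at months 3, 12 and 24 and are not described as specific to an arm.

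**The concern.** The rule places two filters in front of the data.

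The first is attribution. The participant decides whether an event is related before anything is recorded. The design is open label, participants are told that Nordic walking would do them good (Study procedure), and the article expects no harm. An event that the participant does not link to the study falls outside the rule, and so does any healthcare use that follows from it.

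The second is the arm. Patients with type 2 diabetes can be expected to have falls, musculoskeletal complaints and hypoglycaemia without any exercise programme. A count in the walking arms alone therefore has no background rate beside it and cannot be read as harm or as its absence. Controls are not unexposed either: the Study procedure section says they are required to increase physical activity freely. Randomization supplies the comparator, and the rule does not use it.

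There is also a tension with blinding. Randomization and blinding keeps outcome assessors unaware of allocation. A question put at follow-up assessments in only two of three arms requires whoever asks it to know the arm.

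**Working it through.** The article gives no adverse-event rate and no safety power, so there is no stated figure to reproduce. The check is mainly a reading of the text, with simple arithmetic for size.

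**Step 1: which arms does the rule cover?** The trial is described as follows: "A three-arm randomized controlled trial will assess the impact of a primary care-based PA intervention implementing SENWI against an isolated NW programme", with usual advice as the second comparator. The word both cannot mean three arms. The same part of the article shows what it refers to: "Both intervention (NW and SENWI) sessions will be implemented in the surroundings of the different CAP/hospital facilities". When the authors mean all arms there, they say so: "all three interventions have no expected harmful effects as they only involve low- and moderate-intensity PA". The likelier reading is therefore NW plus SENWI.

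Share of participants outside formal collection on that reading: 48 / 144 = 33%.

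**Step 2: does another enquiry close the gap?**

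| Enquiry | Attribution filter | Arms reached | Period | Stated to be recorded as adverse events |
|---|---|---|---|---|
| Follow-up assessments | Yes, by the participant | NW and SENWI (likelier reading) | T1, T2, T3 | Yes |
| Weekly physiotherapist questions | No | NW and SENWI in practice | 12-week programme | No |
| Monthly calls and messages (PA drop-out ratio section) | Not applicable: they ask about continued physical activity | Not restricted in the text | To 21 months after the intervention | No |

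The unfiltered weekly questions cover about 3 of 24 months: 3 / 24 = 12.5%. For the other 21 months only participant-attributed events are collected.

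**Step 3: what would equal collection allow?** The event rates below are assumptions. The calculation uses a two-sided 5% level, no allowance for dropout, and the normal approximation with pooled variance under the null:

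power = Φ{ [ |p1 − p2| − 1.96 √( p̄(1 − p̄)(1/n1 + 1/n2) ) ] / √( p1(1 − p1)/n1 + p2(1 − p2)/n2 ) }

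For 5% against 15% with 48 per arm, p̄ = 0.10. The first square root is √(0.09 × 2/48) = 0.0612 and the second is √((0.0475 + 0.1275)/48) = 0.0604. Power = Φ{(0.10 − 0.1200)/0.0604} = Φ(−0.33) = 37%.

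| Control vs walking (assumed) | 48 vs 48 | 48 control vs 96 pooled walkers |
|---|---|---|
| 5% vs 15% | 37% | 41% |
| 5% vs 20% | 61% | 69% |
| 5% vs 30% | 91% | 97% |

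Equal collection would give a like-for-like estimate in each arm, but only a large difference would be detected reliably.

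**The case against.** The strongest case against has four parts.

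- **The weekly questions are a real safeguard.** They cover the whole period of supervised exposure and do not depend on attribution. A reader might infer from the formal rule that every unattributed event is lost. The article does not support that for the first 12 weeks, because such events may surface in the weekly enquiry. What remains is that the answers are not said to be recorded as adverse events, the questions stop with the programme, and they do not reach controls, which adds to the unequal ascertainment.
- **The exclusion of controls is an inference.** A reader might take it as a stated fact that controls are never asked. The article does not say so; the phrase is garbled, and the follow-up assessments apply to all arms. The inference is strong, but it remains a reading. If all three arms were meant, the sentence is wrong as written and still needs correction.
- **No planned claim rests on safety.** It is not an aim, a listed outcome, a success criterion or a conclusion. This stands, and it limits the weight of the point. HbA1c, blood pressure, anthropometry, quality of life and medication are not restricted to the walking arms, so some health measures remain comparable. They do not replace adverse events.
- **The direction of bias is not settled.** A reader might infer that attribution can only lower the count. That holds for all-cause events, but unblinded walkers could also attribute ordinary aches to the programme, so the count of events called related could err either way.

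The point is not a mere gap in a condensed article: the restriction is stated.

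**Conclusion.** The concern holds in a limited form. Formal adverse-event collection is restricted to participant-attributed events and, on the likelier reading, to the two walking arms. Followed as written, the plan gives no adverse-event rate for 48 of 144 participants (33%), so harms cannot be set against usual care. Unattributed events after week 12, that is over 21 of the 24 months, are not captured in any arm.

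This rests on two assumptions: that both refers to NW and SENWI, and that the weekly questions reach only those whom the NW physiotherapist sees. It does not undermine the efficacy comparisons. It is a weakness in harms ascertainment that should be corrected because the remedy is cheap.

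**What to change.** At T1, T2 and T3, ask all three arms the same standard question about any adverse event and any related healthcare use, whatever the participant thinks caused it. Record relatedness as a separate field and report events by arm. Because the weekly questions reach only the walking arms, report events found only through them separately, and base between-arm comparisons on the common T1 to T3 enquiry. Replace the phrase about both groups with an explicit list of arms. An identical question in every arm also removes the need for the person asking to know the allocation.

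The cost is a few extra questions at assessments that already take place, with no added visits. The comparison should be labelled descriptive, given the low power for modest differences. Trial status reports 40 volunteers enrolled at submission, with recruitment still to start at four of the five sites. On those figures 144 − 40 = 104 participants could be covered from entry, and those already enrolled could be asked at their remaining assessments.

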### Comparator group 1: NW programme

Before the intervention, participants will do a beginner’s class in NW over 2 days with an instructor. This will be done at the same place where the intervention will be conducted (i.e. outdoors near the CAPs). After these two sessions, the 12-week intervention with two sessions/week will start. Sessions will be progressive: the first month will last for 30 min, the second month 35 min and the third month 40 min (plus 10-min warm-up and 10-min cool-down in each session). Track paths will be flat and will not have more than 100-m cumulative altitude. The meeting point will be at the CAP facilities.

Participants will be scheduled at two different times (e.g. midday and afternoon). Each group will receive 26 NW sessions. Patients will receive a schedule with all 12-week sessions.

### Comparator group 2: usual health care advice

The control group will receive the usual HCP’s advice on PA, health and illness management. This consists of checking up on the results of their blood analyses, asking questions about their day-to-day life, receiving HCP advice on how they should cope with hyperglycemia through diet and trying to encourage patients to walk and integrate more physical activities into their daily routines. Thus, HCP advice is grounded in general recommendations regarding PA and its importance, and not in how, when, where and with whom to do it.

### Intervention group: SENWI programme

Intervention group based on SEM will apply NW like the comparison group 1, but in this group instructors will add the SEM approach. The SEM approach is based on the *Caminemos!* (let’s walk!) protocol with adaptations to be applied in patients with T2DM [48, 49] (see Tables 1 and 2).

**Table 1 Tab1:** General information about the study intervention

Name of the programme	Programme components	Person in charge of Training	Duration	General structure of each session
Comparator group 1	Increase PA levels throughout a NW protocol.	Physiotherapist instructor of NW.	12 weeks. Two sessions of NW per week of 30–40 min. 21-month post-intervention follow-up.	All sessions will begin with a 10-min warm-up focusing on joint mobility. The main session will last between 30 min (first month), 35 min (second month) and 40 min (third month). All training sessions will end with a 10-min cool-down using stretching of the lower limbs.
Intervention group	Raising awareness of the psychological and social importance of PA. Facing socioeconomic barriers to improve PA levels over time.	Physiotherapist instructor of NW trained from a SEM approach.	12 weeks. Two sessions of NW per week of 30–40 min. 21-month post-intervention follow-up.	All sessions will begin with a 10-min warm-up focusing on social and physical interactions and themes per week to work on (see Table L). The main session of NW will last between 30 min (first month), 35 min (second month) and 40 min (third month). All training sessions will end with a 10-min cool-down focusing on social interactions between participants, themes per week to work on and instructors answering questions.
Comparator group 2	Common approach used in healthcare.	HCP that is used to attending T2DM patients.	12 weeks and a 21-month follow-up	Common approach used in healthcare: recommendation to do more PA and walk more.

*PA* physical activity, *NW* Nordic walking, *SEM* socio-ecological model, *T2DM* type 2 diabetes mellitus

**Table 2 Tab2:** Main themes to work on each week and curriculum objectives

Themes per week	Objectives
1–2	Introduce the idea that being physically active should be part of normal ageing and should continue at any age and in any health condition (e.g. T2DM). Teach that ageing or T2DM itself does not cause decreased PA. Identify barriers to being more physically active. Differentiate between modifiable (e.g. psychological) and unmodifiable (e.g. sociological) causes.
3–4	Reinforce the idea that being physically active should be part of everyday normal life and should continue under any circumstances. Identify common changes associated with T2DM and teach that with modifications one can resume an active life.
5–6	Teach that being unable to learn a new habit is not caused by T2DM or ageing. Introduce the idea of SEM. Reflect on whether expectations and beliefs about T2DM have changed. Enhance social networks that support PA
7–8	Reinforce key concepts. Identify positive aspects about being physically active and negative aspects about not being physical active. Problem-solve on how to maintain a PA over time. Enhance social networks that support PA.
9–10	Reinforce the idea that being physically active should be part of everyday normal life and should continue under any circumstances. Identify barriers to being more physically active. Enhance social networks that support PA
11–12	Reinforce key concepts. Problem-solve on how to maintain a PA over time. Make individual commitments to increase PA taking into consideration psychological and social barriers. Enhance social networks that support PA

*PA* physical activity, *T2DM* type 2 diabetes mellitus, *SEM* socio-ecological model. Adaptation from *Caminemos!* (Let’s walk!) protocol [46]

To deliver this model, instructors will be formed by the principal investigator. In each session, the instructors will give small talks and lead a group discussion about the key themes before, during and after the SENWI programme. Themes are divided into three general blocs: enhance the need to do PA continually throughout life, problem-solve on how to maintain PA over time and enhance sociability and social networks that support PA. Moreover, during the first two weeks participants will be asked to report the reasons for being insufficiently active in order to enhance the need to do PA, and then they will be taught to categorize the reasons as either modifiable (e.g. not having a partner to exercise with) or nonmodifiable (e.g. being old or having a medical condition). Then, participants will be asked to find solutions to different problems together as a group, and to explain how to address the modifiable reasons for being insufficiently active. Finally, in each session participants will be asked to establish action plans to increase PA and made commitments to do a specific action before the next meeting (e.g. take my grandson to school on foot). All participants will be encouraged to write down how much “exercise” they do each day and comment at the beginning of each session on how well they kept their commitment. They will also be asked to record any barriers and enablers that they encountered, as well as the extent to which they were able to overcome these barriers.

